### Strategies to improve adherence to interventions {11c}

In order to improve adherence to the intervention requirements and to increase the completion of assessments, all surveys and study information will be sent directly to participants’ smartphone devices. Participants will receive weekly SMS messages with reminders and links to the podcasts included on the app. Surveys will be sent to participants via SMS at each of the assessment timepoints. Participants will be sent reminder messages if they do not complete the surveys within a set time period.

### Relevant concomitant care permitted or prohibited during the trial {11d}

Participants will continue to receive their routine medical care throughout the study period, regardless of being randomised to the intervention or control arm.

### Provisions for post-trial care {30}

The data collected in this study is not expected to cause significant distress or discomfort to participants. However, in the event that participants experience distress in the course of this study, the participant information sheet will provide participants with information about support services they can contact. This will include Beyond Blue, Lifeline, and the research team. In addition, participants who score highly on the EPDS scale, or noted on this scale that they have thought of self-harm, will be flagged by the research team, and further support will be offered.

### Outcomes {12}

Postnatal depression will be the primary outcome of the study. This will be measured using the Edinburgh Postnatal Depression Scale (EPDS). The primary outcome will be EPDS measured at 6 months postpartum. Changes in postnatal depression over time will also be assessed and will be determined by conducting the EPDS at four timepoints: 16 weeks’ gestation, 28 weeks’ gestation, 3 months postpartum, and 6 months postpartum. Secondary outcomes measured at the same timepoints will include measures of mother-infant bonding (using the *Mother-to-Infant Bonding Scale*), quality of life, and cost-effectiveness (using the *PROMIS Global-10*). The primary timepoints for these assessments will be timepoint 1 (16 weeks’ gestation) and timepoint 4 (6 months postpartum). Mindful attention (using the *Mindful Attention Awareness Scale*) will be measured at times one and four. Participant satisfaction with the app (using a bespoke survey described below) will be measured at the third timepoint (3 months postpartum), and participant adherence (measured with click analytics to detect the frequency of app use) will be examined once participants have completed the study (see Fig. 1). The study will also use click analytics to determine the frequency of app use. Demographic data and medical health information will be extracted from medical records for the purposes of inferential statistical analyses. Changes from timepoint 1 will be assessed for all health-related, repeated surveys. Measures will be analysed in aggregate form.

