#### Mother-to-infant bonding scale

The Mother-to-Infant Bonding Scale is an 8-item questionnaire, which asks participants to rate their feelings about their child, to assess the level of bonding [30]. The scale presents participants with eight adjectives (e.g. loving, resentful, disappointed). Participants score how often they feel these adjectives about their child within the first few weeks. Items are scored from 0 to 3 (0 = “not at all”, 1 = “a little”, 2 = “a lot”, 3 = “very much”). Items that indicate positive emotions about the mother’s child are reverse scored (i.e. 0 = “very much”, 3 = “not at all”). A higher total score on this scale indicates lower mother-infant bonding.

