## Statistical methods

### Statistical methods for primary and secondary outcomes {20a}

The primary analyses will be conducted according to the intention-to-treat principle. This means that participant data will be analysed based on the initial treatment assignment and not the treatment ultimately received. Descriptive statistics (mean/standard deviation, median/range, proportion/percentage) will be used to describe participants’ characteristics. Normality testing by visual assessment of the data will precede inferential statistical tests of continuous outcomes, such as questionnaire scores. The primary analysis of EPDS scores at 6 months postpartum will be conducted using a linear regression model to compare the intervention and control groups. This will be analysed using an independent samples *t*-test and further sensitivity analyses using analysis of covariance (ANCOVA) to determine the impact of the intervention on EPDS scores while controlling for covariates such as age and parity.

The mean change in EPDS from timepoint 1 to timepoint 4 will also be investigated. To estimate the changes within and between test groups at each timepoint, a linear mixed effects model for repeated measures will be used. The participant will be treated as a random effect, by means of the restricted maximum likelihood method (REML). The main effects of group, time, and a group-time interaction will be analysed. To determine the effect of the baby’s sex (which will only become known at timepoint two) on outcomes, the main effects of knowledge, sex, and a knowledge-sex interaction will also be measured. Additional potential covariates (age, parity, marital status, child disability, stillbirth or infant death, and previous episode of depression) will be included as fixed effects. Secondary outcomes of interest (mother-to-infant bonding, quality of life, and mindful awareness) will be analysed with the same strategy described above.

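### The bonding scale is scheduled at two antenatal visits and analysed as change from 16 weeks' gestation, although the protocol describes it as rating feelings about the child in the first few weeks

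*Protocol article*

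**What the plan says.** Four statements in the protocol article bear on this point.

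- **Schedule.** Outcomes {12} describes "conducting the EPDS at four timepoints: 16 weeks’ gestation, 28 weeks’ gestation, 3 months postpartum, and 6 months postpartum". It continues: "Secondary outcomes measured at the same timepoints will include measures of mother-infant bonding". Bonding is therefore collected twice before birth and twice after.
- **Primary timepoints and change.** The same section says of the secondary outcomes: "The primary timepoints for these assessments will be timepoint 1 (16 weeks’ gestation) and timepoint 4 (6 months postpartum". It adds: "Changes from timepoint 1 will be assessed for all health-related, repeated surveys".
- **Instrument.** The section Mother-to-infant bonding scale describes a questionnaire "which asks participants to rate their feelings about their child, to assess the level of bonding", and says of the recall period: "Participants score how often they feel these adjectives about their child within the first few weeks". It mentions no wording for pregnancy and no antenatal validation. The EPDS section, by contrast, states that the EPDS has been validated both before and after birth.
- **Analysis.** Statistical methods {20a} says: "Secondary outcomes of interest (mother-to-infant bonding, quality of life, and mindful awareness) will be analysed with the same strategy described above". For the EPDS, that strategy has three parts: a between-group comparison at 6 months postpartum, the mean change from timepoint 1 to timepoint 4, and a linear mixed model over the repeated visits with group, time and group-by-time effects.

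**The concern.** Eligibility {10} admits women at under 16 weeks' gestation, so every participant is pregnant at timepoint 1 and no infant exists at timepoint 1 or 2. A scale described as rating feelings about the child in the first few weeks has no evident referent at those visits. If women do answer it, they answer about something else: expectation, or attachment to the pregnancy. A score of that kind is not a baseline for postnatal bonding.

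Improving mother-baby bonding is the first secondary objective named in Objectives {7}, and the Discussion rests part of the app's potential benefit on it. A reported improvement or decline in bonding since 16 weeks would invite a reading that the measurements cannot support.

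**Working it through.** **Step 1: the plan's own figure.** Inputs from Sample size {14}, which concern the EPDS only: d = 0.50, two-sided 5% level, 80% power, 1:1 allocation, 40% attrition. A two-sample t-test needs 63.77 per arm, so 64 per arm and 128 in total. Then 128 / (1 − 0.40) = 213.3, rounded up to 214. Both stated figures reproduce. Neither depends on the bonding schedule, and the article states no effect size or power for bonding.

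**Step 2: schedule against instrument.**

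| Visit | Before or after birth | Fits the scale as a measure of feelings about a born child? |
|---|---|---|
| 16 weeks' gestation (timepoint 1, a primary timepoint) | before | no |
| 28 weeks' gestation (timepoint 2) | before | no |
| 3 months postpartum (timepoint 3) | after | yes |
| 6 months postpartum (timepoint 4, a primary timepoint) | after | yes |

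Two of the four assessments, including the baseline for change, come before birth.

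**Step 3: what each planned analysis gives for bonding.**

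- Between-arm comparison at 6 months: uses timepoint 4 only, so it is unaffected.
- Arm differences at 3 or at 6 months from the mixed model: interpretable as differences in bonding at those visits.
- Within-arm change from timepoint 1 to 4, and the time effect across birth: these subtract one construct from another, so they are not interpretable as change in bonding.
- Group effect averaged over all four visits: mixes two constructs.
- Between-arm contrast in change: if timepoint 1 answers precede any effect of the app, randomisation makes the expected arm difference at timepoint 1 zero. Then E[contrast in (T4 − T1)] = E[contrast at T4] − 0, and the contrast is unbiased. Only its precision is in question.

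**Step 4: precision of the change contrast (illustration).** With equal variance σ² at both visits and correlation r between them, Var(T4 − T1) = 2(1 − r)σ². The effective standardised difference is d / √[2(1 − r)]. Taking d = 0.50 and 64 per arm from the EPDS calculation:

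| r (assumed) | 2(1 − r) | Effective d | Power |
|---|---|---|---|
| 0 | 2.0 | 0.354 | 51% |
| 0.3 | 1.4 | 0.423 | 66% |
| 0.5 | 1.0 | 0.500 | 80% |
| 0.6 | 0.8 | 0.559 | 88% |

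Timepoint 4 alone gives 80%. The change score therefore loses power below r = 0.5, breaks even at 0.5 and gains above it. The article gives no r.

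**The case against.** The strongest reply is that little is lost. Bonding is secondary, and the strategy it inherits already starts with a between-arm comparison at 6 months, which needs no antenatal score. This stands, and it limits the point to the change and repeated-measures analyses.

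A reader might infer that the antenatal items cannot be answered at all, or that the antenatal assessments are simply invalid. The article does not support that. The adjectives it gives as examples could be applied to an unborn baby, the app includes exercises directed at the unborn baby, and the description of the scale does not say in words that it is for use after birth. What the text supports is narrower: the recall period reads as postnatal, and no antenatal adaptation or validation is stated. Taken literally, the first few weeks match neither 3 nor 6 months well. At those visits, however, there is at least a child to rate.

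A reader might also infer that the whole bonding analysis is meaningless, or that power falls from 80% to about 50%. The first fails because the 6-month comparison and the unbiasedness of the arm contrast in change both survive. The second is only the r = 0 end of a range, computed with figures borrowed from the EPDS.

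Two further defences carry less weight. Fig. 1 is not shown and might give another schedule, but it would then contradict explicit text. The sentence on change speaks of health-related surveys and may not cover bonding. The primary-timepoints sentence and the shared analysis strategy bring bonding into the change analysis without it.

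**Conclusion.** The concern holds, and the plan should be corrected. The article schedules the bonding scale at two visits that its own description does not fit, makes one of them a primary timepoint, and carries bonding into a change analysis from that visit. Within-arm change from 16 weeks, the time effect across birth and a group effect pooled over four visits cannot be read as change in bonding. No value of r repairs this if the constructs differ.

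The damage is contained. The EPDS primary outcome, the sample size and the 6-month between-arm comparison of bonding do not change. The arm contrast in change is unbiased, provided that timepoint 1 answers precede any effect of the app. Its loss of precision ranges from substantial to none, depending on a correlation that the article does not give. The conclusion rests on reading the stated recall period as postnatal and on the absence of any antenatal version in the text.

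**What to change.** - Give the Mother-to-Infant Bonding Scale at 3 and 6 months postpartum only, and amend Outcomes {12} accordingly.
- Make the between-arm difference at 6 months the bonding outcome, with 3 months supportive.
- State that bonding is excluded from changes from timepoint 1, and from the timepoint 1 to timepoint 4 part of the strategy in Statistical methods {20a}.
- If bonding during pregnancy is of interest, name a separate antenatal measure and analyse it as its own outcome, not as a baseline for this scale.

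Adjusting for baseline EPDS, or rewording the recall period for the postpartum visits, is optional. Rewording would raise a validity question of its own.

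The cost is a change to the survey schedule and a few sentences of text, with fewer items for participants at two visits. The downside is that this scale would yield no antenatal data. Trial status puts the start of recruitment in November 2023. The schedule is best settled before baseline surveys go out, because a baseline collected with an unsuitable instrument cannot be repaired afterwards.

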**Fig. 1 Fig1:**
[figure not shown]
Schedule of enrolment, interventions, and assessments according to the SPIRIT 2013 guidelines

### Participant timeline {13}

See the participant timeline in Fig. 1.

### Sample size {14}

The necessary sample size was calculated using the public access software G*Power 3.1.9.7 for Windows [20]. The primary outcome of depression, as measured by the EPDS, was used to estimate the required sample size. Previous meta-analyses that found mindfulness in the perinatal period reduced depression scores with an effect size of *d* = 0.59 [21, 22]. The sample size calculation was therefore based on the estimation of a medium intervention effect (*d* = 0.50). A sample size of 128 was required to compare differences at timepoint 4, with 80% statistical power, a two-tailed significance level of 5%, and a 1:1 allocation ratio. Previous studies have reported high attrition rates of 20–45% [23, 24]. Accounting for an attrition rate of 40%, a final sample size of 214, with 107 individuals in each group, will be required.

### Recruitment {15}

The study will recruit women for up to 3 months, or until the sample size is achieved. The study site manages the treatment of over 800 women per month. Given the sample requirement is less than half this amount, we anticipate achieving full recruitment within 2 months.

## Assignment of interventions: allocation

### Sequence generation {16a}

Participants will be randomly allocated to intervention or control using computer randomisation software, with a 1:1 allocation ratio. A permuted block randomisation technique (block size = 10) will be conducted to ensure assignment of participants will be even across the two groups. Randomisation will be stratified by the midwifery model of care.

### Concealment mechanism {16b}

Allocation will be concealed until assignment occurs. Consenting participants will be assigned an identification number associated with their midwifery model of care for stratified randomisation, on entry into the study. This number will be associated with a pre-defined allocation group determined by computer-generated permuted block randomisation. Recruitment and randomisation will be conducted by separate members of the research team. As such, the investigator randomising the participants will not be aware of previous or forthcoming participant allocation.

### Implementation {16c}

Randomisation will be conducted by an investigator who is not involved in recruitment or data collection. Participant information and consent SMS messages will be sent via the survey software. Upon participant enrollment and allocation, the randomisation number will be given to the investigator overseeing the distribution of the intervention.

## Assignment of interventions: blinding

### Who will be blinded {17a}

Care providers will not be aware of the assignment status of participants. Trial participants will not be blinded to their group allocation status. A member of the research team, not involved with patient care, recruitment, or group allocation, will email the intervention group instructions for downloading the online app and will provide technical assistance to participants. The data analyst will be blinded to participant allocation.

### Procedure for unblinding if needed {17b}

All participant responses will be identified with a numerical pseudonym. A coding key will be kept separate from responses in a password-protected file on the private hospital computer network. Should it become necessary, this coding key can be accessed to identify participants.

## Data collection and management

### Plans for assessment and collection of outcomes {18a}

Data will be collected through Red Cap surveys, via focus group interviews, from online medical databases, or via the app. All surveys (EPDS, PROMIS Global 10, the Mother-to-infant Bonding scale, the Mindful Attention Awareness scale, and the satisfaction survey) will be created in Red Cap survey software. Links to these surveys will be automatically sent to, and completed by, participants via SMS sent directly to their phones. The focus group interviews will collect further data relating to participant satisfaction. The online App will only collect data relating to rates and frequency.

#### The Edinburgh Postnatal Depression Scale (EPDS)

The EPDS is a 10-item questionnaire designed to screen women for symptoms of depression in the postnatal period [25]. Women completing the EPDS are asked to rate the option that best describes how they have felt in the past 7 days in response to a number of statements (e.g. “I have blamed myself unnecessarily when things went wrong.”). Items are scored on a 4-point scale, with response scores ranging from 0 to 3. Item scores are summed to produce a total score. Scores ranging from 0 to 9 indicate low levels of distress, scores from 10 to 12 indicate the presence of distress, and scores above 13 suggest a high presence of depressive symptoms. A minimum 4-point change in scores across timepoints is necessary to be deemed clinically significant [26]. The EPDS has been validated for use in both a prenatal and postnatal population [25, 27]. Women who score one, two, or three on item 10 (“The thought of harming myself has occurred to me”) will be addressed with further enquiry and support if necessary [28].

#### Patient-Reported Outcomes Measurement Information System Global Health Scale (PROMIS Global-10)

The PROMIS Global-10 is a 10-item questionnaire measuring the quality of life through a range of domains, including mental health, physical health, satisfaction with social relationships, and engagement with daily activities [29]. The first nine questions on the scale are rated on a 5-point Likert scale. Questions one to six are rated from “poor” (1) to “excellent” (5); question seven is rated from “not at all” (1) to “completely”; question eight is rated from “always” (1) to “never” (5); and question nine is rated from “very severe” (1) to “very mild” (5). Question 10 is rated on a 10-point scale, asking participants to rate pain on a scale of 1 (“no pain”) to 10 (“worst pain imaginable”). When scoring, scores on question 10 are converted onto a 5-point scale using the table provided in the scoring manual. Participants’ scores on this scale are summed to produce a raw total score. Raw scores are converted into *t*-scores for interpretation against a standardised average score. A score above 50 indicates higher than average quality of life, while a score below 50 indicates lower than average quality of life.

#### Mother-to-infant bonding scale

The Mother-to-Infant Bonding Scale is an 8-item questionnaire, which asks participants to rate their feelings about their child, to assess the level of bonding [30]. The scale presents participants with eight adjectives (e.g. loving, resentful, disappointed). Participants score how often they feel these adjectives about their child within the first few weeks. Items are scored from 0 to 3 (0 = “not at all”, 1 = “a little”, 2 = “a lot”, 3 = “very much”). Items that indicate positive emotions about the mother’s child are reverse scored (i.e. 0 = “very much”, 3 = “not at all”). A higher total score on this scale indicates lower mother-infant bonding.

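### The bonding scale is described as covering the baby's early weeks but is scheduled at 3 and 6 months postpartum; the reference period should be reconciled with the visits

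*Protocol article*

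**What the plan says.** The section on the Mother-to-infant bonding scale gives one reference period and no variant for later visits: "Participants score how often they feel these adjectives about their child within the first few weeks".

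Outcomes {12} sets the schedule. The EPDS is given at four points: "16 weeks’ gestation, 28 weeks’ gestation, 3 months postpartum, and 6 months postpartum". Bonding follows it: "Secondary outcomes measured at the same timepoints will include measures of mother-infant bonding". For the secondary measures the section adds: "The primary timepoints for these assessments will be timepoint 1 (16 weeks’ gestation) and timepoint 4 (6 months postpartum"). It also plans change scores: "Changes from timepoint 1 will be assessed for all health-related, repeated surveys".

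Statistical methods {20a} carries the EPDS analysis over to bonding: "Secondary outcomes of interest (mother-to-infant bonding, quality of life, and mindful awareness) will be analysed with the same strategy described above". That strategy comprises a group comparison at 6 months, the change from timepoint 1 to timepoint 4, and a mixed model with group, time and their interaction.

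The EPDS section gives that scale a period that moves with each visit. Women report "how they have felt in the past 7 days".

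**The concern.** A scale used repeatedly to follow a changing state needs a reference period that moves with the visit. The EPDS has one. The bonding scale, as described, is tied to a fixed early period that is over before either postnatal assessment. A woman who follows that instruction at 3 months and again at 6 months rates the same weeks twice.

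Bonding is the first secondary objective listed in Objectives {7}, and the Discussion counts better bonding among the possible grounds for benefit. The app's content runs to 6 months after birth and includes exercises done with the baby. An effect that builds up over those months is what a 6-month measurement should pick up, and a question about the early weeks is poorly suited to doing so. Participants also know their allocation (Who will be blinded {17a}), so a rating of feelings from months ago could be coloured by having used the app or by present mood.

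**Working it through.** The protocol gives no figure to reproduce. The check compares the reference period with the visit schedule.

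**Inputs from the document**
- Bonding scale: a fixed early period whose starting point is not stated.
- Visits: 16 and 28 weeks' gestation, 3 and 6 months postpartum.
- EPDS: the 7 days before each visit.

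**Assumptions, not in the document**
- The period starts at birth.
- It lasts between 2 and 6 weeks, taken as about 0.5 to 1.5 months (4 weeks to the month).

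**Recall distance** = age of the baby at the visit − end of the reference period.

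| Visit | 6-week window | 2-week window |
|---|---|---|
| 3 months postpartum | 3 − 1.5 = 1.5 months | 3 − 0.5 = 2.5 months |
| 6 months postpartum | 6 − 1.5 = 4.5 months | 6 − 0.5 = 5.5 months |

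Across this range the period is over by both visits, so the qualitative conclusion does not depend on the exact length assumed.

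**What each planned bonding analysis would then rest on**
- *Group comparison at 6 months:* feelings in the early weeks, recalled after about 4.5 to 5.5 months. At the same visit the EPDS describes the preceding 7 days.
- *3-month and 6-month values in the mixed model:* the same target recalled at two distances. A difference between them would largely reflect recall rather than change in bonding.
- *Change from timepoint 1:* at 16 weeks' gestation a period that starts at birth has not begun. The same holds at 28 weeks. The baseline for this change score therefore does not fit the described period either.

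No section of the article adapts the period to the visit.

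**The case against.** The strongest reply is that the sentence in the scale section is a loose summary of the instrument and not the stem shown to women. It uses the present tense, it speaks of frequency although the response options are intensities, and it never says that the period starts at birth. The same section opens by saying simply that the scale rates a mother's feelings about her child. The actual survey text sits in the trial's REDCap forms, which are not shown, and it may already ask about current feelings. This stands, and it makes the point conditional. It does not remove it: if the sentence is only a paraphrase, the article still states a reference period that conflicts with its own schedule.

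A reader might infer that the scale cannot measure bonding at 6 months at all, that the true change between the two postnatal visits is zero by construction, or that the bonding objective is lost. The documents do not support these readings. They require every woman to follow literally a stem that has not been seen. Recall coloured by present mood would also carry some information about the present, although with bias. And app content starts in the second trimester, so a real effect on early bonding could still show in a group comparison at 6 months. The contrast between 3 and 6 months is not singled out in the plan; it is one estimate within the mixed model.

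Fig. 1 is not shown and might restrict the bonding visits. The text, however, names "timepoint 4 (6 months postpartum") as primary for this measure.

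**Conclusion.** The point holds in a conditional form. The stated reference period conflicts with the stated visits, and nothing in the article reconciles them. If the described wording is what women receive, and the period runs from birth, both postnatal scores describe the same early weeks at a distance of about 1.5 to 2.5 and 4.5 to 5.5 months. Later effects on bonding would be poorly captured and the ratings exposed to recall bias, while an effect on early bonding would remain detectable.

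This is a conflict between two stated rules, not a detail left to an analysis plan. It should be corrected, but its reach is limited: the primary EPDS outcome, the sample size and the randomisation are untouched.

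**What to change.** Check the stem in the REDCap survey first. If it already asks about current feelings, only the scale description in the article needs correcting.

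Otherwise, at timepoints 3 and 4 use a stem that asks how the woman feels about her baby now, for example over the past 7 days to match the EPDS. State that period in the scale section and report the adaptation.

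The cost is one line of survey text, one sentence of protocol wording, and some loss of comparability with the published scale.

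If the stem as described must be kept, label the 3-month and 6-month scores as recalled early bonding. Do not interpret them as bonding at 6 months or as change between the postnatal visits. The 6-month group comparison need not be dropped.

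In the same revision, state whether the scale is given before birth. If it is, say with what reference period; if it is not, remove timepoint 1 as a primary timepoint and as the baseline for change in bonding.
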